### Intervention

#### Dietary intervention

All women will receive standard GDM dietary advice in line with evidence-based guidelines [2, 40, 43, 44]. Women will be encouraged to consume a minimum carbohydrate intake of 175 g per day, from mostly low glycaemic sources, distributed across the day over three meals and three snacks. The dietary advice will promote a low saturated fat intake and higher consumption of vegetables, fruit, dairy and whole grains.

After Baseline data are collected, women who are randomised to either of the two dietary intervention groups (RS Diet & RS Supp) will receive additional dietary education on consuming a high RS diet commencing on Day 3. All RS dietary education will be conducted by the PI who is an experienced Accredited Practising Dietitian (APD). A standardised teaching plan (Supplement 3) and education materials will be utilised (Supplements 4 & 5). Participants will be provided with written material including a Gut Feeling cookbook [45] and sample menus, as well as some non-perishable samples of high RS foods to allow for immediate adoption of the diet. Dietary RS will be measured at Baseline, Day 10 and Day 56 using 3-day weighed food records (Supplement 6). Evidence of compliance with the high RS diet will also be monitored via urine samples for metabolomic analysis and change in stool microbiota at the same timepoints. Participants will be asked to continue the high RS diet until the delivery of their child.

The RS education tools and strategies have been piloted in a non-pregnant population and achieved a median increase in dietary RS intake of ≥6.6 g RS per day (unpublished data). The typical intake of RS in Australian women aged 19–44 years has been estimated to range from 2.9–8.3 g per day [46]. Similarly, recent data from the United States estimated the mean daily intake of RS to be 1.9 g per 1000 kcal for women of this age [47], which would equate to 3.8–5.7 g per day.

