### Secondary outcomes

#### Post-prandial glucose

Post-prandial blood glucose (PPBG) will be measured by participants using SMBG three times per day for three consecutive days. The change in mean 2-h PPBG and frequency of PPBG levels above the target for each mealtime will be calculated and compared within and between groups at Baseline (Day 1–3), Days 8–10 and Days 54–56. Two-hour PPBG excursions of 6.7 mmol/L or more are considered above the target for optimal pregnancy outcomes [49]. Elevated PPBG are associated with preeclampsia, caesarean section delivery, large for gestational age (LGA), neonatal hypoglycaemia [6] and childhood glucose and IR [10].

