### Statistical analyses

Baseline demographic and outcome variables will be described and compared for differences between groups. Continuous variables will be described as mean ± standard deviation (SD) and nominal and ordinal variables as frequencies and proportions. All continuous variables will be examined for normality using the Shapiro-Wilk test. Descriptive statistics for non-normal continuous variables will be presented as median ± interquartile range (IQR).

FBG and PPBG will be monitored on the first 2 days and averaged to provide a Baseline measure of each outcome. These will be compared to those measured over the subsequent 8 days, and then again between Days 48 and 56, across the three dietary groups (Control, RS Diet and RS Supp) using linear mixed modelling with group-by-time interaction. Analysis will assess if a 0.3 mmol/L reduction is achieved. Demographic variables such as age, pre-pregnancy BMI, parity and ethnicity will be adjusted in the model. Statistical analyses will be performed using SPSS® (Statistical Package for Social Sciences, version 27 for Windows).

The number of PPBG excursions experienced by a participant per day between Days 4 to 10 will be examined and compared relative to the number determined at their Baseline over the first 2 days of the usual care diet. Generalised Mixed Modelling will be utilised to assess whether a dietary change reduces the frequency of PPBG excursions as compared with norm with adjustments for relevant demographic variables.

Different R packages and PRIMER 7 (Quest Research, NZ), a non-parametric statistical software package, will be used to assess change within and between groups for microbial composition. Distance Based Linear Modelling (DistLM) will be used to look for a correlation between change in stool microbiota or SCFA & measures of glycaemia.

Direct and indirect costs savings related to any reduction in insulin treatment or improvements in maternal and neonatal outcomes will be calculated from DRG codes, Weighted Activity Units (WAU) and the National Efficient Price (NEP) and reported [74].

Missing data will be treated in statistical analysis as missing and coded as 999 or left blank, so as not to affect the accuracy of the analysis. Prior to any statistical analysis, all data will be explored for outliers. Any outliers found will be cross-checked with the source file. Any true outliers will be checked with the clinician before being removed/left in the dataset.

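### The stated analysis of post-prandial excursions is a before-after contrast over Days 4-10, although the outcome section promises a between-group comparison at other windows

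*Protocol article*

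**What the plan says.** Two sections of the protocol article deal with how often post-prandial glucose is above target.

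- **Secondary outcomes, Post-prandial glucose.** "The change in mean 2-h PPBG and frequency of PPBG levels above the target for each mealtime will be calculated", and these are to be "compared within and between groups at Baseline (Day 1–3), Days 8–10 and Days 54–56". Target is breached at 6.7 mmol/L or more at 2 hours.
- **Statistical analyses, third paragraph.** "The number of PPBG excursions experienced by a participant per day between Days 4 to 10 will be examined". The reference for this count is the woman herself before the RS diet starts: it is "compared relative to the number determined at their Baseline over the first 2 days of the usual care diet". The model follows: "Generalised Mixed Modelling will be utilised to assess whether a dietary change reduces the frequency of PPBG excursions as compared with norm", with adjustment for demographic variables.

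The paragraph just before the excursion paragraph handles fasting and post-prandial glucose levels differently. Those are compared "across the three dietary groups (Control, RS Diet and RS Supp) using linear mixed modelling with group-by-time interaction", and its windows include Days 48 to 56.

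On what the arms share, the Dietary intervention section says: "All women will receive standard GDM dietary advice in line with evidence-based guidelines". The Fasting blood glucose section adds self-monitoring education as routine. RS education for the two intervention arms starts on Day 3, after Baseline.

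**The concern.** The trial randomises women to Control, RS Diet or RS Supp, and only a comparison with Control can separate RS from whatever happens to every newly diagnosed woman in her first days of standard advice and self-monitoring. The excursion paragraph does not state that comparison. Its reference is the woman's own first 2 days, and its follow-up window begins the day after RS education, so the contrast it describes is before against after the start of the RS diet.

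If the analyst follows that wording, a fall that also occurred in Control could be reported as an effect of the RS diets. The Day 54-56 comparison promised in the outcome section would also have no stated analysis.

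**Working it through.** **1. The passages side by side**

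| Item | Post-prandial glucose section | Statistical analyses, excursions | Statistical analyses, glucose levels |
|---|---|---|---|
| Contrast | Within and between groups | Own baseline, *norm* | Three arms, group-by-time |
| Baseline | Days 1-3 | First 2 days | First 2 days |
| Early window | Days 8-10 | Days 4-10 | Subsequent 8 days |
| Late window | Days 54-56 | None | Days 48-56 |

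The two sections on excursion frequency disagree on the contrast and on every window. Days 1-3 also include the day RS education begins; the first 2 days do not.

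**2. What each contrast estimates**

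On the model's link scale, let δ be the change common to all arms and θ the added RS effect, taken as equal in both RS arms. Arms are of equal size.

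- Before-after within an RS arm: δ + θ.
- One time term over all three arms with no group term: (δ + (δ + θ) + (δ + θ))/3 = δ + (2/3)θ, approximately.
- Group-by-time, RS arm against Control: (δ + θ) − δ = θ.

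Only the third is free of δ. The second also dilutes a true RS effect by a third.

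**3. Precision given up**

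Let σ² be the variance of a woman's change and n the number per arm. Before-after in one arm has variance σ²/n. RS arm against Control has σ²/n + σ²/n = 2σ²/n, so its standard error is √2 ≈ 1.41 times as large.

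**4. Illustration of the risk**

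The plan gives no figure for this analysis: no excursion rate, spread or expected change in Control. Everything here except the arm size and the number of readings is assumed. Inputs: 23 women per arm (Sample size section); 3 post-meal readings a day, hence 2 × 3 = 6 at baseline and 7 × 3 = 21 on Days 4-10; 30% of readings above target at baseline; woman-level probabilities beta-distributed with concentration 6; the same proportional fall in all arms; no RS effect; 4,000 simulated trials per row. Tests are at 5%: a one-sample t-test on change in the RS arms, and a one-way comparison of change across the three arms.

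| Shared fall | Before-after, RS arms pooled | Before-after, one RS arm | Between arms |
|---|---|---|---|
| None | 4.5% | 5.2% | 5.0% |
| 30% to 25% | 39% | 20% | 5.4% |
| 30% to 20% | 93% | 63% | 5.0% |
| 30% to 15% | 99.8% | 94% | 5.3% |

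These falls are 5/30 = 17%, 10/30 = 33% and 15/30 = 50% in relative terms. A second set of assumptions (log-normal rates around 0.9 excursions a day, log SD 0.6) gives 17%, 52% and 87% for the pooled before-after test at relative falls of 10%, 20% and 30%, with the between-arm test again near 5%. The before-after rate depends on the assumed fall. The between-arm rate does not.

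**The case against.** The strongest reply is that the between-group comparison is already in the protocol: the outcome section says the "frequency of PPBG levels above the target for each mealtime will be calculated and compared within and between groups". The analysis paragraph gives no formula or list of terms, so its silence on group need not mean that group is left out, and an article may leave the full term list to an analysis plan. *Norm* could mean usual care, that is, Control. A dietary change could be the exposure itself, since only the RS arms change diet after Baseline. Baseline is taken on the usual care diet, so part of any shared response may already have happened by then.

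Much of this stands. A reader might infer that the model excludes a group term and that a shared fall will be credited to RS. The documents do not establish either, because the outcome section promises the between-group comparison and *norm* is open to more than one reading. A reader might also take the simulated rejection rates as the false-positive rate of this plan. They are not: they come from t-tests confined to the RS arms, which the protocol does not describe (it names a generalised mixed model), and from assumed rates and falls.

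The disagreement between sections remains. The adjacent paragraph names the arms and the interaction where that contrast is meant; the excursion paragraph names a different reference and different windows. That is more than brevity. Even if dietary change is coded as the exposure, Control's change is removed only if a time term is fitted beside it, and none is stated.

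**Conclusion.** The point holds as an inconsistency that should be fixed. The outcome section commits to a between-group comparison at three windows; the only stated analysis is a comparison with own baseline at two, with an undefined reference. Followed literally, it estimates the RS effect plus any change shared with Control, so a shared fall could be credited to the RS diets.

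A shared fall is plausible from the design, but the document supports no figure for it. The direction of the problem rests only on the algebra; its size cannot be derived.

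The consequence is limited. This is one part of a secondary outcome, and both fasting glucose, the primary outcome, and post-prandial glucose level have a stated group-by-time interaction across the three arms.

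**What to change.** Replace the excursion sentences in Statistical analyses with wording such as:

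> Excursion frequency (readings above target out of readings taken) will be analysed in a generalised linear mixed model on all three arms, with group, time, group-by-time and a participant random effect, adjusted for age, pre-pregnancy BMI, parity and ethnicity. The RS effect is the group-by-time contrast of each RS arm against Control. Change from a woman's own baseline is descriptive only.

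Drop *norm*. State one set of windows, including whether Day 3 belongs to Baseline and whether Days 54-56 are analysed, and use it in both the Post-prandial glucose and Statistical analyses sections.

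The change needs no new data and no different class of model. Its cost is precision: the standard error is about 1.41 times that of a before-after test in one arm. That is the price of a contrast that isolates RS from standard care.

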Gut microbiota and glycaemic control are known to be altered by fermentable dietary fibres such as resistant starch (RS) [28, 29, 37, 38]. A systematic review by Colantonio, Werner and Brown [29] concluded that foods with prebiotic properties, such as RS, may improve glycaemic control in women with T2DM. More specifically, a meta-analysis of RS supplementation by Wang et al. [28] showed improvements in fasting glucose and IR, particularly in overweight or obese people with diabetes. Microbial fermentation of RS increases the production of short chain fatty acids (SCFA) [39]. SCFA are thought to improve glycaemic control through multiple mechanisms [20], discussed later, suggesting that the manipulation of the microbiome using RS may be a novel therapeutic option for reducing the severity of GDM.

This study will evaluate whether a high dietary RS intake from diagnosis with GDM can improve maternal glycaemic control; impacts the maternal and/or neonatal gut microbiota, faecal SCFA production, maternal and neonatal health outcomes; and collect information to determine the health economic benefits of improvement of dyads health outcomes that result from this intervention.

We hypothesise that compared with standard GDM dietary advice, women with a high dietary intake of RS from the diagnosis of GDM will show a reduction in fasting blood glucose (FBG) levels and other measures of glycaemic control. This will reduce the percentage of women who require insulin and improve maternal and foetal outcomes.

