#### RS supplement

The RS Supp group will consume an RS supplement of high-amylose maize (HAMS) type 2 resistant starch. Participants will be given a 600 g tub of HAMS each fortnight, along with a 40 ml scoop. They will be instructed and provided with written material (Supplement 7) on how to prepare and incorporate the RS supplement into cool fluids or foods in their diet. As with all low-digestible carbohydrates, gastrointestinal (GI) discomfort is a known side effect of rapid introduction of RS, therefore, participants will introduce HAMS over a two-day adjustment period. They will be instructed to consume 1 scoop (20 g) per day for 2 days, taking half in the morning and the rest at night. Then, increasing to a dose of 1 scoop (20 g) morning and night for the remainder of their pregnancy. The RS supplement contains 40% RS type 2. The final amount of RS in the 40 g of HAMS per day will be 16 g, which is below the level of 45 g per day of RS supplementation that is known to be tolerated with minimal side effects, most of which are flatulence [48]. Intakes of up to 80 g RS per day have been tolerated without diarrhoea [48]. Those in the high RS diet plus RS supplement are unlikely to achieve this amount. Consumption and compliance of the RS supplement will be monitored by weight of unconsumed HAMS returned fortnightly. Participants will use a daily RS supplement diary to record intake as an additional measure of compliance. We have shown in a recent 2-week feasibility study, 100% compliance with consumption of the RS supplement and minimal GI side effects in 10 female participants with prediabetes or T2DM (unpublished). GI tolerance of the supplement will be measured via a daily bowel symptom diary for the first 10 days and Days 47 to 56.

Participants can withdraw from the study at any time for any reason. Participants will be withdrawn by the investigator if they commence antibiotics, steroids, metformin or if they can no longer comply with the study’s schedule of assessments (Table 1).

**Table 1 Tab1:** Participant measurements and collection summary

	Day 1	Day 3	Day 10	Day 28	Day 42	Day 56	Day 7 post-partum
Recruitment & consent	√						
Randomisation of subjects	√						
Attend clinic	√	√	√		√	√	
Self-monitoring blood glucose data collection		√	√			√	
FreeStyle Libre Pro application	√				√		
Questionnaires:							
medical Hx	√						
medication	√						
GI symptoms	√		√			√	
Quality of Life SF36	√		√			√	
Weight measured	√		√			√	

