#### Maternal and neonatal outcomes and cost of antenatal care

Maternal and neonatal outcomes data will be collected from the DMR after discharge. Diagnosis Related Group (DRG) [74] data will be collected for calculation of hospital costs. Maternal outcome data collection will include the number of ANC clinic visits, Maternal Foetal Assessment Unit visits, antenatal admissions, delivery method, post-partum maternal length of stay, and feeding method on discharge.

After discharge, data on admission to the Neonatal Intensive Care Unit (NICU), reason for admission and length of stay will be collected from the DMR of the infant to determine the frequency of admissions to NICU in the intervention groups compared to the control group. NICU admission for neonatal hypoglycaemia or respiratory support is a known complication in babies of GDM mothers and is one of our secondary outcomes for the study. There is a linear relationship between glycaemia and admissions to NICU in offspring of women with GDM [6]. We will record this outcome and collect neonatal samples as and when the baby’s clinical condition allows. We accept that research on pregnant women raises particular safety concerns. It is noteworthy that our intervention is safe and we do not expect serious adverse events as a direct result of the intervention. We expect neonatal deaths to be not different from the general population.

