A limitation of this study is that food will not be provided to the participants which may limit compliance with a high RS diet. However, a positive result would indicate that this dietary intervention is a practical and achievable intervention to incorporate into GDM management strategies. Periodic assessment of glucose is also a limitation of the study as it only estimates overall glycaemic control but is the most frequently used method in the management of GDM, whereas continuous blood glucose monitoring would assess the overall exposure of the foetus to glucose. Funding for continuous blood glucose sensors is not yet available, therefore, an opportunity to identify any overall glycaemic benefit through time-in-range values may be missed. The study is adequately powered to detect improvements in FBG and microbial changes (based on changes in faecal SCFA) but not for other outcomes such as rates of LGA, macrosomia, neonatal hypoglycaemia and NICU admissions.

This will be the first study to evaluate RS intervention in GDM management. If a high dietary intake of RS is shown to favourably alter the GDM microbiome and results in improved glycaemic control, this will expand the dietary interventions available to manage GDM without pharmacotherapy, reducing the burden on the mother and the healthcare system. If a more favourable maternal gut microbiota is found to persist post-partum and is transferred to the neonate, longer-term health outcomes for mother and child may be enhanced.

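### The economic result is worded as gross savings only and no cost of the RS interventions is set against them, so as stated it favours RS, most of all RS Supp

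*Protocol article*

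**What the plan says.** The protocol article deals with health economics in three places.

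- **Background** gives the aim: to "collect information to determine the health economic benefits of improvement of dyads health outcomes that result from this intervention".
- **Maternal and neonatal outcomes and cost of antenatal care** describes the data. "Diagnosis Related Group (DRG) [74] data will be collected for calculation of hospital costs". It continues: "Maternal outcome data collection will include the number of ANC clinic visits, Maternal Foetal Assessment Unit visits, antenatal admissions, delivery method", and further items such as length of stay. NICU admissions are to be compared between the intervention groups and Control.
- **Statistical analyses** states the result to be reported: "Direct and indirect costs savings related to any reduction in insulin treatment or improvements in maternal and neonatal outcomes will be calculated". Three price sources are named there: DRG codes, WAU and NEP.

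The resources used only by the RS arms are described elsewhere. Under Dietary intervention, both RS arms receive additional education from a dietitian, a cookbook, sample menus and samples of high-RS foods. Under RS supplement, the RS Supp arm also receives high-amylose maize starch (HAMS) until the end of pregnancy: "Participants will be given a 600 g tub of HAMS each fortnight". None of these items appears in a cost calculation.

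**The concern.** Two features of the stated result lean the same way.

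1. **It is gross.** What the RS arms consume and Control does not is left out. The named price sources are for hospital activity, and no source is named for an issued supplement, cookbook or food sample. The omission is larger in RS Supp than in RS Diet, so it also distorts the comparison that the Discussion presents as unique to this study: whether whole foods suffice or a supplement is needed.
2. **It is worded in one direction.** Savings, reductions and improvements are named. Increases in insulin use and worse outcomes are not.

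The outcomes to be priced are also noisy. The Discussion says the trial is adequately powered for fasting glucose and microbial changes "but not for other outcomes such as rates of LGA, macrosomia, neonatal hypoglycaemia and NICU admissions". Chance differences will occur in both directions, so how unfavourable ones are handled matters.

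At stake is whether the reported figure can inform a decision to adopt either intervention. A gross saving cannot, however carefully the hospital items are priced.

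**Working it through.** The article gives no unit cost, expected saving or threshold, so there is no planned figure to reproduce. The check asks what the stated quantity would show if RS had no effect.

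**Step 1. Effect of omitting the intervention cost.** Let S be the gross saving per mother-infant pair (Control minus RS, hospital items and insulin) and I the intervention cost per pair.

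- True net saving = S − I. Reported saving = S.
- Overstatement = S − (S − I) = I, whatever the effect of RS.
- With no effect and signed counting, E[S] = 0. The report shows break-even; the truth is −I.
- I in RS Supp = I in RS Diet + the cost of HAMS, so RS Supp gains most from the omission.

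Quantity of HAMS: one 600 g tub per fortnight. Assuming 8 to 16 weeks of use (4 to 8 fortnights), 4 × 600 g = 2.4 kg to 8 × 600 g = 4.8 kg per woman. No price is given.

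**Step 2. Effect of counting only favourable differences.** This applies only if the wording is taken literally.

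Inputs:
- Arm size n = 30 randomised, or 23 after attrition (Sample size section).
- Insulin rate p = 0.5 in every arm. This is an assumption, guided by the Background's statement that in some populations more than half of women need pharmacotherapy. The range 0.3 to 0.6 was also run.

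Let D = (X_C − X_RS)/n, with X_C and X_RS independent Binomial(n, p). Exact results for n = 30, p = 0.5:

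| Quantity | Result |
|---|---|
| Signed counting, E[D] | 0 |
| Probability that a given RS arm has fewer insulin users than Control | 0.449 |
| Favourable-only counting, E[max(0, D)] | 0.0513, i.e. 5.1 percentage points |
| Probability that at least one of the two RS arms shows a reduction | 0.613 |

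Normal check: SE of D = √(2 × 0.5 × 0.5 / 30) = 0.129; E[max(0, D)] ≈ 0.129/√(2π) = 0.129 × 0.399 = 0.0515, in agreement.

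Across n = 23 and 30 and p = 0.3 to 0.6, the apparent reduction is 4.7 to 5.9 points and the probability for at least one arm is 0.598 to 0.613.

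**Step 3. Which reading does the text support?** Statistical analyses names only favourable changes. The section on maternal and neonatal outcomes collects DRG and resource-use data with no restriction to women who improve, and compares NICU admissions with Control. Requirement for insulin treatment likewise compares insulin use with Control. A signed difference can be computed from the planned data, and the text does not settle which is meant. Step 1 applies on either reading; Step 2 on one.

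**The case against.** A reader might infer that the analysis will show a saving even if RS does nothing. The documents do not support that as a general statement. It requires unfavourable differences to be dropped, and no section says they will be. The reference to any reduction can equally mean whatever signed reduction is found. On that reading the expected gross saving under no effect is zero, and a given RS arm is more likely than not to show no insulin reduction (1 − 0.449 = 0.551). Omitting the intervention cost then hides a loss; it does not create a saving. This part of the objection stands.

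A reader might also take the Discussion's call for a cost-effective lifestyle solution as a claim this analysis is meant to prove. It describes what the field needs. The Background aim is to collect information on benefit, and no cost-effectiveness ratio or net-benefit estimate is promised. This stands too: a hospital-only calculation is legitimate if it is labelled as one.

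The last defence is that a journal article gives economics one sentence and leaves perspective and cost items to a fuller plan. That excuses missing detail. It does not dispose of the point, because the quantity that the article does state is gross and worded in one direction. Nor does the article's open admission of limited power, which does not say how unfavourable differences will be costed.

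**Conclusion.** The point holds in a limited form. As stated, the economic result is a gross saving that overstates the net result by the intervention cost on any reading, and by more in RS Supp than in RS Diet. With no RS effect and signed counting, it would show about break-even in place of a net loss equal to that cost. A spurious saving arises only if favourable differences alone are counted; for insulin this is about 5 percentage points per RS arm (4.7 to 5.9 over the ranges examined), under equal assumed insulin rates in all arms. Without prices, neither component can be expressed in money. The primary outcome, sample size and randomisation are unaffected. This is a secondary analysis that should be corrected before costs are reported.

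**What to change.** Restate the economic result in Statistical analyses as the difference between arms in mean cost per randomised mother-infant pair, RS Diet against Control and RS Supp against Control, with a confidence interval.

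- Count increases as well as decreases in insulin use and in the resource items already collected: antenatal and assessment-unit visits, admissions, delivery, NICU admission and length of stay.
- Add the RS intervention cost: dietitian time, written materials and cookbook, food samples, and HAMS issued. Name a price source for each.
- If the intervention cost is not included, call the result a gross hospital cost difference and draw no cost-effectiveness conclusion from it.

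The hospital data are already planned, and the supplement is issued in weighed portions with returns weighed. The added work is a change of wording and a small tally of resources issued. The price is a reported saving that will be smaller and less certain.

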### Sample size

In a study by Asemi et al. [42], the average woman with GDM has a mean FBG of 5.175 ± 0.86 mmol/L. In RS supplementation trials, a difference in FBG as large as 0.4 mmol/L has been observed between control and RS supplemented groups [38]. This study aims to demonstrate a reduction in FBG of 0.3 mmol/L, which corresponds to a small to medium Cohen’s effect size (*d* = 0.35). Based on a repeated-measures design with three groups (Control, RS Diet, RS Supp) and three time points (Baseline, Day 10 and approximately Day 56), a minimum sample size of 69 (i.e., 23 per group) is required to detect a small to medium within-between interaction effect (Cohen’s *f* = 0.175) at 80% power and 5% level of significance. Allowing for an attrition rate of around 30%, the final total sample size required is 90 (i.e., 30 per group). Women who commence insulin therapy will remain in the study.

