### Randomisation

Stratified randomisation of participants based on pre-pregnancy Body Mass Index (BMI) category will be utilised. BMI categories are Healthy (BMI 18.5–24.9 kg/m^2^), Overweight (BMI 25–29.9 kg/m^2^) and Obese (BMI ≥ 30 kg/m^2^). A computer-generated random sequence was created by a statistician and repeating blocks of three groups per three BMI categories were used to generate group allocation order. Eligible participants will be randomised by the PI to the next predetermined group, sequentially as consented. Neither the participants nor the investigators will or can be blinded to the treatment allocated.

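### In an open-label trial, outliers confirmed against source may still be deleted after a clinician's check, with no criterion and no masking

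*Protocol article*

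**What the plan says.** The last paragraph of Statistical analyses sets out three steps.

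1. Screening: "Prior to any statistical analysis, all data will be explored for outliers". This covers the primary outcome.
2. Source check: "Any outliers found will be cross-checked with the source file".
3. Decision: "Any true outliers will be checked with the clinician before being removed/left in the dataset".

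Because the source check comes first, the natural reading of a true outlier is a value that the source has confirmed. The text offers both removal and retention and does not say what decides between them.

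On blinding, the Randomisation section states: "Neither the participants nor the investigators will or can be blinded to the treatment allocated". It also has the principal investigator allocate each woman. The Dietary intervention section has the same person give all the resistant starch education.

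The Fasting blood glucose section under Primary outcome makes reduction in FBG the primary outcome. It describes FBG above target as the measure hardest to control by diet and the one most likely to signal a need for medical therapy.

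**The concern.** Correcting a transcription error improves the data. Deleting a value that the source has confirmed removes information. Here the values most likely to be flagged are high FBG readings, and a genuine high FBG is a poor response on the primary outcome.

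If the person who decides knows the arm, removal can differ between arms without any intent to mislead, for example by finding a high value more surprising in a resistant starch arm than in the control arm. Differential removal biases the between-group difference. Even balanced removal of real extremes shrinks the observed variance and makes standard errors too small. The screening is to be done before analysis, which hides the results from the decision-maker but not the allocation.

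**Working it through.** **Inputs from the Sample size section.** The SD is 0.86 mmol/L ("the average woman with GDM has a mean FBG of 5.175 ± 0.86 mmol/L"). The target is 0.3 mmol/L ("This study aims to demonstrate a reduction in FBG of 0.3 mmol/L"). The plan needs 69 evaluable women (23 per arm) and enrols 90 (30 per arm), allowing about 30% attrition.

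**Reproducing the plan's own figures.**
- Effect size: 0.3/0.86 = 0.35, as stated.
- Sample size: a noncentral F calculation for the group-by-time interaction used f = 0.175, three groups, three time points and a 5% level. The within-person correlation is not stated; 0.5 and sphericity were assumed. Power is 0.811 at N = 69 and 0.790 at N = 66, so 69 is reproduced in multiples of three.
- Attrition: 90 × 0.7 = 63, or 21 per arm. The evaluable number per arm therefore plausibly lies between 21 and 30.

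**Shift from one deletion.** If a value lies z SDs above its arm mean, removing it lowers that mean, and so changes the between-arm difference, by z × SD/(n − 1). With z = 3 (assumed), the numerator is 3 × 0.86 = 2.58.

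| Per arm | Shift (mmol/L) | Share of 0.3 |
|---|---|---|
| 30 | 2.58/29 = 0.089 | 30% |
| 23 | 2.58/22 = 0.117 | 39% |
| 21 | 2.58/20 = 0.129 | 43% |

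Measuring the distance from the mean of the remaining values gives z × SD/n instead, for example 2.58/23 = 0.112 (37%).

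**Sensitivity to the assumptions.**
- Distance: at 23 per arm, a 2 SD value gives 0.078 (26%) and a 4 SD value 0.156 (52%). A shift above 0.1, one third of the target, needs about 2.56 SD at 23 per arm, 2.33 at 21 and 3.37 at 30.
- SD: an assumed SD of 0.5 gives 3 × 0.5/22 = 0.068 (23%).
- Change from baseline: the SD of a change is 0.86 × √(2(1 − ρ)). A 3 SD change at 23 per arm then shifts the mean by 0.139 at ρ = 0.3, 0.117 at 0.5 and 0.091 at 0.7.
- Daily readings: the Statistical analyses section also describes FBG over eight days after the baseline days. With 23 × 8 = 184 readings, equal weights and SD 0.86 per reading, one deleted 3 SD reading moves the arm's mean for that period by 2.58/183 = 0.014 (about 5%).
- Median: in a simulation of normal samples with 23 per arm, dropping the highest value moved the median by about 0.05 on average and the mean by about 0.075.

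**Error rate.** A simulated two-arm t-test under the null with 23 per arm had a two-sided type I error of about 5% with all data kept. It was about 6.6% when the highest value in one arm was always dropped, and about 11% when the lowest value in the other arm was dropped as well.

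**The case against.** Several points on the other side have force.

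- **The size depends on the analysis.** The simple arm-mean formula is not the planned model. A mixed model on daily readings would dilute one deletion to about 0.014 mmol/L. With one value per visit, the model still keeps the woman's other visits. The Primary outcome section also words the endpoint as a median. All of this stands, so the 30% to 43% is an illustration for one venous value per visit. A reader might infer that one deletion always moves the result by more than a third of the target. The documents do not support that, even on the venous basis: at 30 per arm it takes more than 3 SD or more than one deletion.
- **The clinician is not said to be an investigator or to see allocation, and electronic data are kept de-identified.** This is correct. A reader might infer that people who know the arm will make the deletions; the text only leaves that open. De-identified storage does not by itself mask the arm.
- **A clinician's check can be useful.** A sample not taken fasting would agree with its source and still not be an FBG. This stands, and the fix must allow for it.
- **Outlier definitions and sensitivity analyses usually belong in the SAP.** Their absence alone is no finding. The point here is the permission that the article does state.
- **The missing-data code.** A reader might infer that the 999 code could enter the analysis as a glucose value. The text says otherwise: "Missing data will be treated in statistical analysis as missing and coded as 999 or left blank, so as not to affect the accuracy". The outlier screen in the same paragraph would also catch a glucose of 999, so nothing is claimed on that score.

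**Conclusion.** The concern holds as a fault in the stated rule. Followed as written, the plan permits source-verified primary-outcome values to be removed case by case, without a criterion and without masking, in an open-label trial where a high FBG is itself the outcome of interest.

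The possible effect ranges from small to material. It is 0.09 to 0.13 mmol/L against a target of 0.3 if one venous value per woman per visit is analysed and one value 3 SD out is deleted, with SD 0.86 and 21 to 30 women per arm. It is much less if daily readings or a median are used. The gain in false-positive risk from a single one-sided deletion is modest; the larger figure of about 11% needs selective removal in both arms. The documents do not say that any value will be removed, or that removal will differ by arm. The weakness is that nothing in the rule prevents it.

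**What to change.** Replace the last sentence of the paragraph with a rule to this effect, fixed before any outcome data are screened:

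- All values that are confirmed against source and are valid measurements stay in the primary analysis.
- Only documented recording, assay or sampling-validity errors (for example, a sample not taken fasting) are corrected or set to missing. The decision follows a pre-set rule and is made without sight of allocation, with the reason logged.
- Any exclusion of verified outliers, or a robust version of the mixed model, is reported only as a sensitivity analysis beside the primary result.

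The clinician's check remains, but its question becomes whether the measurement is valid, not whether it is extreme. For verified, valid values, the discretionary shift in the primary analysis becomes zero.

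The cost is a few sentences in the protocol or SAP, a masked listing for the clinician and one extra sensitivity run. Standard errors may be slightly larger because genuine extremes are kept.
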